Third, we recognize that genetic susceptibility contributes to the development of some diseases and the patients’ response to therapy [8]. Indeed, some patients with paroxysmal AF will not progress to persistent AF for many years while others progress more quickly. Stroke also happens in some AF patients without any known risk factors. Incorporating phenotype and genotype studies will provide the opportunity for better understanding of AF as a disease entity and for personalized treatment.

The Chinese Atrial Fibrillation Registry study (CAFR) is a prospective registry study launched in August 2011 and is still ongoing. Herein we reported the rationale, design of this study and current status of the database.

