### Statistical analysis

The CHADS_2_ schema and CHA_2_DS_2_-VASc schema will be compared and validated in these Chinese AF patients, after excluding patients receiving anticoagulation therapy or ablation therapy during follow up. Logistic regression will be used to evaluate the predictive value of the various risk schemata in discriminating between patients who develop the outcome of interest and those who do not. The c-statistic will be estimated to determine the predictive ability for stroke of each schema. The 95 % confidence interval will be estimated for the c-statistic using a non-parametric bias-corrected bootstrapping method. To assess the effect of individual risk factors on the occurrence of events, multivariable logistic regression will be used with the baseline covariates as independent variables. According to the result of the multivariable logistic regression analysis, the score for each risk factor will be adjusted for the best fitted classification schema. If necessary, new risk factors may also be added to generate a new stroke risk classification schema for Chinese AF population. The new schema will be validated on the validation population and the C-statistics will be calculated using the new risk schema. In addition, the net reclassification index will also be used to evaluate predictive value of the prognostic score.

To compare the ablation and non-ablation therapies, propensity score matching for receiving catheter ablation will be calculated for each patient based on a multivariable logistic regression model. Baseline characteristics variables which are assumed to be associated with the probability of having catheter ablation will be included in the model as independent variables. Based on the propensity scores, ablation and non-ablation patients will be matched on a 1:1 basis with a combination of the nearest neighbor algorithm and caliper algorithm [12]. For each ablation patient, a non-ablation patient with the smallest propensity score difference, and smaller than 0.02, will be matched without replacement. Patients not matched will be excluded from the analysis.

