### Sample size calculation

For the objective of developing the optimal risk prediction model for Chinese AF population, a minimum of 200 events (i.e. 10 times of the variable number) are required to accommodate 20 variables in the prediction model. The analysis is planned to be done in 2015 to accumulate enough events for analysis. For that purpose, about 5000 patients without anticoagulation therapy are required for an evenly splitted training cohort and validation cohort. For the objective of evaluating the effectiveness of ablation therapy, the following assumption is made: the accumulate ischemic stroke and intracranial hemorrhage is 10 % in optimally anticoagulated patients and 7 % in ablation patients in five years, 1800 matched patients in each arm are required to provide 90 % power to detect the difference (α = 0.05). As those two groups of patients are quite different, we amplified the sample size by 3 times to guarantee enough matched patients. In total, 16000 patients are required for the main analyses and considering a possible 20 % withdraw and loss of follow up, we up round the sample size to 20000.

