## Results

### Current status and data quality

17467 patients had been enrolled as at June 30, 2015. The majority (84.0 %) came from tertiary hospitals where most AF patients are managed. The missing rates for the key variables are listed in Table 3. There are no missing data among the mandatory variables which is controlled by the EDC system. Out of range variables were very rare (<0.1 %) for those with range check. Patient follow up rates at 6, 12, 18 and 24 months are 93, 91, 87 and 85 % respectively.

**Table 3 Tab3:** Variables collected in the CAFR study and missing rate for each key variables

Variables	Number of variables currently collected	Missing rate (%)
Age or Date of Birth	17467	0 %
Sex	17467	0 %
Date of initial register	17467	0 %
Type of AF	17340	0.73 %
Systolic blood pressure	17291	1.01 %
Height	15845	9.29 %
Body weight	15964	8.60 %
History of alcohol-drinking	17250	1.24 %
History of hypertension	17331	0.78 %
History of diabetes mellitus	17331	0.78 %
History of hyperlipidemia	17288	1.02 %
History of heart failure	17331	0.78 %
History of myocardial infarction	17328	0.80 %
History of coronary artery disease	17330	0.78 %
Signs of heart failure	17329	0.79 %
Hemoglobin level	13552	22.4 %
Creatinine level	14264	18.3 %
Fasting blood glucose	13718	21.4 %
Total cholesterol	13587	22.2 %
Is thyroid function within normal range	12367	29.2 %
Left ventricular ejection fraction	13568	22.3 %
History of direct current cardioversion	17268	1.14 %
History of radiofrequency ablation	17332	0.77 %
History of ischemic stroke/transient ischemia attach/ peripheral arterial thromboembolism	17338	0.74 %
History of intracranial hemorrhage/other major bleeding	17335	0.76 %
Use antiarrhythmic agents	17334	0.76 %
Use ventricular rate control agents	17332	0.77 %
use antithrombotic agents	17333	0.77 %
Warfarin	17281	1.06 %
Use Angiotensin converting enzyme inhibitors/angiotensin receptor blockers	17281	1.06 %
Use Statins	17283	1.05 %

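### The stroke-score analysis fixes a binary logistic model with no time horizon, although follow-up at the 2015 analysis can run from zero to about four years

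*Protocol article*

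**What the plan says.** The Statistical analysis section of the protocol article sets the method for comparing CHADS2 and CHA2DS2-VASc and for building a Chinese score: "Logistic regression will be used to evaluate the predictive value of the various risk schemata". The contrast is binary: patients with the event against patients without it. Discrimination follows: "The c-statistic will be estimated to determine the predictive ability for stroke of each schema". For individual risk factors, "multivariable logistic regression will be used with the baseline covariates as independent variables", and the points of the adjusted or new score come from that fit. A net reclassification index is added. No prediction horizon, minimum follow-up, follow-up-time term, censoring rule or treatment of death is attached to any of these steps.

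The timing is given elsewhere in the article:

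- **Background:** CAFR "is a prospective registry study launched in August 2011 and is still ongoing".
- **Patient inclusion and exclusion criteria:** enrolment stops at 20000 patients, with no calendar date.
- **Sample size calculation:** for the prediction model, "The analysis is planned to be done in 2015 to accumulate enough events for analysis".
- **Current status and data quality:** 17467 patients were enrolled by 30 June 2015. The entry beginning "Patient follow up rates at 6, 12, 18 and 24 months" gives 93, 91, 87 and 85%.

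For the ablation comparison, the same Statistical analysis section specifies time to first event with Kaplan-Meier and log-rank methods.

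**The concern.** Ordinary logistic regression estimates the probability of an event over one common period in which every patient is fully observed. This cohort has no such period. Enrolment had been open for nearly four years and was not finished when the analysis was due, and the analysis was timed by the accumulation of events.

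Under the stated model, a stroke-free patient enrolled in spring 2015, one lost after six months, one who died without a stroke and one followed for nearly four years all contribute the same non-event. Dropping the short-follow-up, lost or dead patients instead would select on observation time and also bias the result.

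Validating and improving risk scores is the first main objective, so the quantity at stake is the stroke risk attached to each score level. If it refers to no defined time, it cannot be read as an annual or 2-year risk or set against rates from other cohorts.

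**Working it through.** **The plan's own figure.** 10 events per variable x 20 variables = 200 events, as stated. This figure and the other sample-size figures are not affected by the present point.

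**Span of follow-up.** Inputs: start in August 2011 (Background) and status date 30 June 2015 (Current status and data quality). From 1 August 2011 to 30 June 2015 is 3.91 years; to 31 December 2015 it is 4.42 years. Assume uniform accrual and no minimum follow-up:

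- Under 6 months: 0.5/3.91 = 12.8% (0.5/4 = 12.5% with a rounded four-year window).
- Under 1 year: 1/3.91 = 25.6% (1/4 = 25%).

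These are shares by potential follow-up; losses would add to them.

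**What the crude proportion measures.** Assume a constant stroke hazard h, uniform accrual over T = 3.91 years, and no loss or death.

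- Risk by time t: 1 - exp(-ht).
- Pooled crude proportion: 1 - [1 - exp(-hT)]/(hT).
- Example, h = 0.03: hT = 0.1173 and 1 - exp(-0.1173) = 0.1107, so the crude proportion is 1 - 0.1107/0.1173 = 5.6%.

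| Assumed hazard per year | 1-year risk | Crude proportion | 3.91-year risk |
|---|---|---|---|
| 2% | 2.0% | 3.8% | 7.5% |
| 3% | 3.0% | 5.6% | 11.1% |
| 4% | 3.9% | 7.4% | 14.5% |
| 5% | 4.9% | 9.2% | 17.8% |

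The crude figure is nearly twice the 1-year risk and about half the 3.91-year risk. It would move again with the cut-off date or the accrual pattern.

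**Adding loss and death.** Simulation of one million patients per scenario. Assumptions: stroke hazard 3% per year, log hazard ratio 0.6 per standard deviation of a normal risk score, death 3-5% per year, loss of 15% by 24 months (matching the reported 85%), uniform entry over 3.91 years.

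- Observed stroke proportion: about 1.4-1.5% in patients with under 1 year of possible follow-up, and 7.5-8.0% in those with over 3 years.
- Of the patients counted as having no stroke, 19-22% had died or been lost.

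**Discrimination.** The benchmark is the c-statistic for stroke within 2 years with everyone followed and no deaths, 0.666-0.668. The binary c-statistic was:

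- 0.664 with death unrelated to the score (a fall of 0.004);
- 0.656 with 3% death per year rising with the score (0.011);
- 0.650 with 5% death per year rising with the score (0.016);
- 0.644 with 5% death rising more steeply (0.023).

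Part of the larger falls comes from competing death itself. A separate set of assumptions (4% stroke, 5% death, 8% loss per year, four-year uniform entry) gave 0.634 against 0.637 when censoring was unrelated to risk. Across these scenarios the change is 0.003 to under 0.03.

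**Point weights.** In a six-factor simulation with true weights 1:1:1:1:2:1 and no link between entry date and risk, the logistic coefficients stood in the ratio 1:0.99:0.98:0.99:1.96:1.03. The integer points are unchanged.

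**When follow-up length is related to risk.** If higher-risk patients enrol later, discrimination falls further. With a six-point score, an entry-score correlation of about 0.2 costs about 0.03 and about 0.3 costs about 0.05. A fall from 0.64 to 0.58 needs drift of that order or stronger.

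**The case against.** **The full plan may settle it.** A journal article condenses, and a horizon, analysis set or censoring rule may stand in the full plan. Only about 5000 patients without anticoagulation are needed, so a subset enrolled early or with a minimum follow-up is possible. This stands in part: no such subset is stated and none is ruled out, so the 12.5-13% under 6 months is conditional. But the article does fix the model, the binary contrast and the source of the points. Adding a horizon would still leave incomplete follow-up and competing death, which ordinary logistic regression does not handle.

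**The stated aim is discrimination.** The section sets out to separate patients with and without events and to compare two schemata in the same patients; it promises no annual or 2-year risk. This also largely stands: discrimination and relative weights are fairly robust here, which limits the severity.

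**Stronger readings that the documents do not support.**

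- A reader might infer that the plan instructs deaths and losses to be coded as stroke-free. No sentence says so. It follows from a binary model with no censoring rule, but it is not a written rule.
- A reader might infer that the c-statistic or the integer points will be badly wrong. That needs follow-up length to be tied to risk, for example by later enrolment of higher-risk patients. Nothing in the article documents such drift, so 0.64 to 0.58 is hypothetical.

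**Conclusion.** The point holds as a badly fixed method: a model without time is specified for a cohort whose follow-up is uneven and incomplete by design. The firm part needs no assumed rates. Enrolment ran from August 2011 and was still open in mid-2015, 15% were not followed at 24 months, and no horizon or handling of censoring and death is attached to the logistic model, c-statistic or net reclassification index.

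The size rests on assumptions. Stroke hazards, death rates and the accrual pattern are not in the article. The principal consequence is that absolute risk and calibration refer to no defined time; the effect on ranking and points is small unless risk and follow-up length are linked. This should be fixed before the score is derived, but it does not by itself invalidate the comparison of the two existing schemata.

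**What to change.** Replace the logistic analyses with time-to-event analyses measured from enrolment:

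- Derive and validate the scores with Cox models, and take the points from those coefficients.
- For absolute risk, use Fine-Gray models or cumulative incidence with death as a competing event.
- Report c-indices with inverse-probability-of-censoring weights (Uno type) at fixed 1- and 2-year horizons. Harrell's index is not a substitute, because it depends on the censoring distribution.
- Compute the net reclassification index in a censoring-adjusted form at the same horizons; as specified it has the same defect as the c-statistic.
- Show observed against predicted cumulative incidence at those horizons.
- State the data cut-off, any minimum follow-up, and how deaths and losses are handled.

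The cost is analysis wording and slightly more analysis work. Event, death and last-contact dates are already needed for the planned Kaplan-Meier analysis of ablation, so no new data are required, and the stated sample sizes do not change.

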### Clinical data collection

Key data elements and definition of each variable were in line with the ACC/AHA recommendation on AF clinical data standards [9] and international peer studies [10] to facilitate cross-comparison of results between different registries. The following data were collected for each patient enrolled: basic socio-demographic information, symptoms and signs relating to AF, medical history, results of physical examination and laboratory test and patient self-reported quality of life (using a validated Chinese version of AFEQT questionnaire). For patients undergoing ablation therapy, detailed procedure related information is also collected, including the pathway of ablation, achievement of conduction block, time consumed and peri-procedure complications.

Each enrolled patient will be followed up every 6 months by trained staff, at outpatient clinic or through telephone interview. Information relating to medical therapies, health-care utilization, and clinical outcomes will be collected during follow up. Definition of the major outcome events are provided in Table 2. Every patient will be followed up until 2020. The questionnaires used for data collection in study are provided in appendix. All the data were entered into a specific electronic data capture system.

**Table 2 Tab2:** Outcomes collected and associated definitions

Outcomes	Definitions
Primary outcome	
Composite outcome of any of the following events: all-cause mortality, non-fatal ischemic stroke and peripheral embolism.	All-cause mortality: All deaths regardless of etiology
	Non-fatal Ischemic stroke: Documented stroke or cerebrovascular accident consisting of acute loss of neurological function caused by an ischemic event with residual symptoms at least 24 hours after onset.
	Peripheral embolism: Abrupt vascular insufficiency associated with clinical and radiological evidence of arterial occlusion in a vascular bed other than the cerebrovascular system in the absence of other likely mechanisms (e.g., atherosclerosis).
Secondary outcomes	
Component of the primary composite outcome including: 1) all-cause mortality; 2) non-fatal stroke or peripheral embolism.	As above
Intracranial hemorrhages	Bleeding into or around the brain, including 1) Hemorrhagic conversion of a primary ischemic stroke; 2) Subarachnoid hemorrhage; 3) Intra-cerebral hemorrhage; 4) Other (including subdural and epidural hematomas);

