Unadjusted event rates for the composite primary outcome of time to first all-cause mortality, stroke and peripheral embolism for the propensity-matched ablation and non-ablation groups will be estimated using the Kaplan-Meier method and compared between groups with the log-rank test. As sensitivity analyses, the inverse probability of treatment weighting using propensity score will also be used to compare the survival distributions between ablation and non-ablation group.

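### The ablation comparison uses fixed groups with no time zero and no rule for ablation after or before enrolment; if status is taken from ablation at any time in follow-up, the result is biased toward ablation

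*Protocol article*

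**What the plan says.** Objective (iii) in Research objectives is to compare ablation with medical therapy for death and thromboembolic events in propensity-matched cohorts. The Statistical analysis section of the protocol article sets this out as follows.

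- **One score per patient:** "propensity score matching for receiving catheter ablation will be calculated for each patient", using multivariable logistic regression.
- **Baseline covariates:** "Baseline characteristics variables which are assumed to be associated with the probability of having catheter ablation will be included in the model".
- **Matching on the score alone:** for each ablation patient, "a non-ablation patient with the smallest propensity score difference, and smaller than 0.02, will be matched without replacement". Time since enrolment is not a matching variable.
- **Outcome analysis:** event rates "for the propensity-matched ablation and non-ablation groups will be estimated using the Kaplan-Meier method" and compared by the log-rank test. The sensitivity analysis is inverse probability of treatment weighting (IPTW) between the same two groups.

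The same section, on the stroke risk scores, restricts that analysis to patients left "after excluding patients receiving anticoagulation therapy or ablation therapy during follow up". The plan therefore recognises that ablation can follow enrolment. Patients are enrolled from outpatient and inpatient settings (Patient inclusion and exclusion criteria), not only at the procedure. After enrolment, "Information relating to medical therapies, health-care utilization, and clinical outcomes will be collected during follow up". Table 3 also lists "History of radiofrequency ablation", so ablation before enrolment is recorded.

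For the ablation comparison the article states no start of the survival clock, no window in which ablation must occur to count, and no rule for patients ablated later or before enrolment.

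**The concern.** Suppose that ablation at any time in follow-up puts a patient in the ablation group. Two errors then act in the same direction.

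1. An ablated patient cannot have died between enrolment and the procedure. If that time is counted, it is event-free by construction.
2. A candidate who dies, or has a stroke that rules out the procedure, while waiting is counted as non-ablation. The control group collects events from patients who were on their way to ablation.

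A baseline propensity score does not remove either error, because both arise after baseline. Matching may even draw in the failed candidates, since at baseline they look like patients who were ablated. IPTW on the same groups inherits both errors. A larger sample only makes the false difference look more certain. At stake is a main objective of the registry: it could report a benefit of ablation where there is none.

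**Working it through.** **The plan's own figure.** Sample size calculation gives 10% v 7% at five years, 90% power, α = 0.05, and 1800 per arm. Two-sided, without continuity correction:

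n = [1.96·√(2·0.085·0.915) + 1.2816·√(0.10·0.90 + 0.07·0.93)]² / 0.03² = (0.773 + 0.505)² / 0.0009 ≈ 1814.

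Power at 1800 is 0.898. The stated figure reproduces and is not in dispute. The implied hazard ratio is ln 0.93 / ln 0.90 = 0.69.

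**Model for the bias (assumptions).** There is no true effect of ablation. Events occur at a constant rate λ of 2.1% (10% in five years), 3% or 5% per year, over T = 5 years from enrolment. Half of the patients are ablation candidates (k = 1 candidate per non-candidate). A share s of candidates is ablated after a wait uniform on 0 to W years, the rest at enrolment. A candidate is classed as ablated only if event-free at the procedure; otherwise he or she counts as non-ablation. The mean delay over all candidates is m = s·W/2.

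**First-order formula.**
- Ablated, clock at enrolment: rate ≈ λ(1 − m/T).
- Non-ablated: rate ≈ λ(1 + k·m/T), because each candidate adds about λm events to this group.
- Ratio with an enrolment clock: (1 − m/T) / (1 + k·m/T).
- Ratio if only the ablated are re-clocked at the procedure: 1 / (1 + k·m/T).

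| Share delayed | Wait up to | m (years) | Enrolment clock, formula | Simulated | Ablated re-clocked, formula | Simulated |
|---|---|---|---|---|---|---|
| 20% | 6 months | 0.05 | 0.99/1.01 = 0.98 | 0.98 | 1/1.01 = 0.99 | 0.99 |
| 20% | 12 months | 0.10 | 0.98/1.02 = 0.96 | 0.96 | 1/1.02 = 0.98 | 0.98 |
| 20% | 24 months | 0.20 | 0.96/1.04 = 0.92 | 0.92 | 1/1.04 = 0.96 | 0.96 |
| 100% | 6 months | 0.25 | 0.95/1.05 = 0.90 | 0.90 | 1/1.05 = 0.95 | 0.95 |
| 100% | 12 months | 0.50 | 0.90/1.10 = 0.82 | 0.80–0.81 | 1/1.10 = 0.91 | 0.90–0.91 |
| 100% | 24 months | 1.00 | 0.80/1.20 = 0.67 | 0.65–0.66 | 1/1.20 = 0.83 | 0.83 |

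Simulated values are rounded and hardly depend on λ. With a quarter of patients as candidates (k = 1/3) and all ablations delayed, the enrolment-clock ratios are about 0.93, 0.86 and 0.74.

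**False-benefit probability.** Take 1800 per arm, a 10% control risk, an enrolment clock and only the first error. With all ablations delayed by up to 24 months, the ablated five-year risk is 8.09%:

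z = (0.1000 − 0.0809) / √[(0.0809·0.9191 + 0.10·0.90)/1800] = 0.0191/0.00956 = 2.00.

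The chance of a significant false benefit is then Φ(2.00 − 1.96) ≈ 51%, against a nominal 2.5%. For waits up to 12 and 6 months (ablated risks 9.04% and 9.51%) it is about 16% and 7%. With 10% of ablations delayed by up to 6 months it is about 3%.

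**The case against.** **No time origin is stated.** A reader might infer from the baseline covariates that patients are followed from registry baseline. The article does not say so; it uses the word baseline only for the covariates. The clock could start at the ablation date, or status could be fixed at enrolment. This stands, and the point is worded conditionally for that reason. But a clock at ablation for the ablated patients alone is not a cure: control patients have no ablation date, failed candidates stay among them, and the ratio is still about 0.95, 0.90–0.91 and 0.83 when all ablations are delayed. Fixing status at enrolment would avoid the bias, but the article does not say that this is done.

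**A condensed article leaves such detail to the full protocol or SAP.** This stands in part, since those documents may define the index date. However, the article does fix the covariates' timing, the matching algorithm, the caliper, the replacement rule, the test and the sensitivity analysis. The method so fixed has no step that aligns the two groups in time, although the same section acknowledges later ablation.

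**The large figures are near-worst cases.** This stands. Eighteen of the 20 tertiary hospitals have ablation facilities, 84.0% of patients come from tertiary hospitals, and inpatients are enrolled. Many patients may be enrolled around the ablation admission, and the bias could then be small.

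**The 7% v 10% benchmark concerns another endpoint.** This stands. Those risks are for ischemic stroke plus intracranial hemorrhage, while the planned comparison is of death, stroke and peripheral embolism. The hazard ratio of 0.69 is only a yardstick.

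**Conclusion.** The point holds in conditional form. The plan fixes static groups, a single baseline score and ordinary survival methods, acknowledges ablation during follow-up, and gives no time zero and no rule for ablation after or before enrolment. If status is taken from ablation at any time in follow-up, the comparison is biased toward ablation, and neither the matching nor the IPTW analysis removes this.

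With an enrolment clock and no true effect, the apparent rate ratio lies between about 0.98 (20% delayed, up to 6 months) and about 0.65 (all delayed, up to 24 months). This rests on the assumed share delayed, the waits, half of the patients being candidates, and an event while waiting ruling out ablation.

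Two stronger readings are not supported. The documents do not show that the bias will equal the planned effect. Nor does it always favour ablation: patients ablated before enrolment contribute no immortal time after it, and the direction of any bias from including them is not established. They need a stated rule for a different reason, namely that they are survivors of an earlier treatment.

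**What to change.** Before the ablation comparison is run, define a common time zero for both groups:

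- Match each patient, at the date of ablation, to a patient who at the same time since enrolment is alive, event-free and not yet ablated. Follow both from that date.
- Base the propensity score on the latest covariates available at that date.
- Exclude patients ablated before enrolment from both groups.
- Keep controls who are ablated later as matched, with a sensitivity analysis that censors them at ablation and weights for that censoring.
- Use the same time zero in the IPTW analysis.

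Fixing status at enrolment or at a landmark, or treating ablation as a time-dependent exposure, would also deal with the problem. Whichever is chosen should be written down, together with the number ablated after enrolment and the distribution of their delays, so that readers can judge how much it mattered.

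The cost is mainly wording and more complex programming; the 1800 per arm calculation does not change. There are three small downsides. Patients ablated before enrolment are lost. Late ablations contribute shorter follow-up. The method relies on the ablation date, which the article does not list by name among the procedure data, and on covariates that may not all be updated at 6-monthly visits, some of which are by telephone. In Table 3 the laboratory values and ejection fraction are already 18.3% to 29.2% missing, so the updated score may have to rest on the history and treatment variables.
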